**Demographics and background history**

- Age, gender, height, weight, bowel history and symptoms, defection disorder diagnosis

**Anorectal manometry measurements**

- Manometry measurements before and after therapy: anal sphincter tone during rest and squeeze, rectal pressure during rest and push manoeuvre, anorectal muscle coordination during push manoeuvre.

**During biofeedback therapy**

- Participants keep a physical or digital bowel diary (bowel habits, stool consistency, symptoms)
- Participants keep a physical or digital food diary (meals, macro nutrients consumes, fibre consumed)
- The Vaizey and Wexner faecal incontinence score completed at the first and last appointment [20, 21]
- A the last appointment, participant provide self-evaluation of treatment efficacy and change [22]

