Home-based BF with training devices has been proposed in the past [14-17]. Studies have demonstrated equivalent efficacy to office-based therapy while being more cost-effective. However, due to technical limitations, these past devices do not have the capabilities for therapists to remotely monitor and track patient compliance, which have significantly limited their adoption into clinical practice.

We have developed a new Internet-of-Medical-Things to deliver home-based BF. The system consists of an insertable probe with sensors to collect data on anal sphincter muscle contractility and rectal lumen pressures. The probe is wirelessly connected to a mobile app to provide real-time visual feedback of muscle activities to the user. The app records and processes training session data and clinical indicators (symptoms & bowel diary) from user input. Processed data will be sent to a cloud server to allow health providers to track progress and aid in decision-making. The proposed device will allow for instrumented anorectal BF training to be performed by patients at home.

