**3. AIMS/OBJECTIVES/HYPOTHESES**

*Aim*

To compare the treatment efficacy of anorectal biofeedback (clinical indicators and physiological parameters) performed with a novel home-based device with conventional therapy options in patients with functional defecation disorders.

*Faecal incontinence is a heterogeneous condition, there is no single parameter to adequately define or represent an optimal way of assessing clinical outcomes. A range of subjective and physiological measures of bowel function are used as outcomes measures.*

*Site 1 Specific* - A feasibility assessment at Site 1 will evaluate the accuracy and repeatability of the prototype (V2) against anorectal manometry*

1. *Evaluate the capability of experimental device to generate anorectal exercise profiles*
2. *Compare the accuracy of experimental device against anorectal manometry*

*Site 1 and Site 2*

*Subjective primary outcome measures*

1. *Vaizey and Wexner faecal incontinence scores*
2. *Faecal incontinent episodes (days per week)*

*Objective primary outcome measure*

1. *Anal sphincter squeeze pressure (mmHg)*

*Secondary outcome measures*

1. *Anal sphincter resting pressure (mmHg)*
2. *Patient’s own view of effectiveness rating (“worse”, “same”, “improved”, or “cured”) and rating of that change in an ordinal scale of – 5 to + 5*
3. *Frequency of bowel motions and symptoms*
4. *[Experimental device group] Usability interview – 1. Ease of use, 2. Clarity of instructions, 3. Ease of cleaning, 4. Any additional Issues*

Hypotheses

We hypothesised that instrumented home BF therapy with the novel device is as efficacious as clinic-based BF therapy

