**5.3 Data source and Population**

*Study population and size*

The Site 1 feasibility study will be a pilot study involving n=15 (n=20 with 33% dropout) participants per group. This study will evaluate the capability of the experimental device to provide instrumented BF (create distinct BF exercise profiles and is understood by the user) and compare the data against anorectal manometry. This is similar to our previous study [18] but will use the new prototype (V2) and be in a patient population.

The data from this site will not be analysed together with data from Site 2, given the differences in methodology. However, data from Site 1 will be used to improve the statistical analysis plan for Site 2. Currently, the power calculations for Site 2 are based on a previous study [19], but data from Site 1 will be integrated to improve the calculation of sample size and power for Site 2.

Site 2 sample size and power calculations

Based on a previous study of biofeedback treatment for faecal incontinence [19], we estimate that for assessing home-BF and clinic-BF efficacy with a sample size of 30 per group (n=40 with 33% dropout), the paired t-test at the 0.05 significance level can detect a mean change in anorectal function measure of at least 0.45 SD with 0.80 power. This corresponds to at least a mean decrease of 8 in Vaizey/Wexner faecal incontinence score, decrease of 0.6 in faecal incontinence episodes, and 40% increase in anal sphincter squeeze pressure.

For the non-inferiority study, based on changes in the primary outcome measures, with n=30 per study arm, the test for non-inferiority has 0.70 power to reject, at the 0.05 significance level, the null hypothesis that the mean change due to home-BF is smaller than clinic-BF by at least 0.44 SD in favour of he alternative hypothesis that mean changes due to home-BF is no more than 0.44 SD lower than clinic-BF (i.e. Ho: ΔHB-ΔOB<−0.44SD vs. Ha: ΔHB-ΔOB≤−0.44SD).

Using estimates from previous study [19], we consider home-BF no worse than or better than clinic-BF if the home-BF group had at least 9 point decrease in Vaizey/Wexner faecal incontinence score (11 for clinic-BF, SD=3), 0.95 days/week decrease in faecal incontinence episodes (1.1 for clinic-BF, SD=0.25), and 19 mmHg increase in anal sphincter squeeze pressure (25 mmHg for clinic-BF, SD=10).

*Data collection/Outcome measurements*

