2. **Squeeze and hold:** The patient is asked to squeeze the anus for as long as possible, for a maximum of 30 seconds. By convention, this manoeuvre is performed three times. Both the maximal contractile pressure and endurance times are measured. Ideally, rectal pressure should not increase, because that would imply the patient has contracted the abdominal wall.
3. **Simulated defecation (push):** The patient bear down as if to defecation and attempt to expel the catheter. This manoeuvre should produce sufficient rectal propulsion pressures with simultaneous anal sphincter relaxation (>20% relaxation).

During treatment period, patients are asked to keep a bowel and food diary. During their in-clinic visits, the therapist will provide consultation on the patient’s progress and any changes to clinical indicators.

*Home-based biofeedback using new device*

In addition to the general instructions, patients selected for home-based BF with novel device (**Group B**) will be trained on the use of home-training device by the therapist. For feasibility study at Site 1, participants will use the device in the clinic under supervision for a maximum of six sessions.

Accuracy and repeatability of prototype V2 will be assessed in the first five (n=5) group B participants. Participant manometry parameters (e.g. resting, push, squeeze) will be compared against the prototype data during their first training session. Capabilities of the V2 sensors will compared against previous V1 data [18] to determine if the V2 prototype is suitable for use. If V2 sensors are not deemed suitable, the trial will be temporary suspended while the technical issues are resolved. During this time, the participant will be removed from the study and begin conventional treatment. If V2 sensors are suitable the participant will continue with trial and subsequent sessions.

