Group B participants will undergo 6 supervised clinic sessions with the experimental device. After session two, they may also take the device home and continue training during the treatment period. The wireless device contains sensors to measure anal sphincter and rectal pressures. A condom sheath is placed over the probe before it is inserted into the anal canal. The user will download the training program (mobile app) onto their mobile phones, which will guide the user through the required exercises (identical to the clinic-based BF manoeuvres listed above). Participants will be asked to insert the probe and perform training for 5 – 10 minutes daily over a training period of 2 months. Training data is send to a cloud server for therapist to monitor compliance and correct usage. The participants are asked to keep daily bowel and food diaries on the app, this information is sent to the cloud accessible only by the therapist and investigators.

Upon completion of the feasibility study, home-based BF with novel device at Site 2 (Group B) will only undergo one supervised training session with the novel device. Participants then take the device home and continue training unsupervised for the duration of their treatment period. The therapist monitor adhesion remotely through the cloud server and will arrange fortnightly telehealth consultations to provide encouragement and evaluate progress.

At the end of the treatment period, participants in Group B will undergo a short useability interview. The therapist will ask the participant questions regarding the 1. Ease of use, 2. Clarity of instructions, 3. Ease of cleaning, 4. Any additional Issues.

*Data analyses*

At the end of the treatment period participants will return to the clinic for a repeat anorectal manometry study to determine changes in anorectal physiology parameters. The therapist will also review their bowel and food diaries. The therapist will discuss the results with the participants and plan the next course of action.

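### Incontinent days per week, a primary outcome judged on a decrease, has no named source and no scheduled pre-treatment count, and the diary form is fixed only for the home arm

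*Protocol*

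**What the plan says.** - **Outcome.** Protocol Section 3 lists "Faecal incontinent episodes (days per week" among the subjective primary outcomes for both sites.
- **Criterion.** Section 5.3 judges it as a change. For Site 2, home therapy is acceptable with a "0.95 days/week decrease in faecal incontinence episodes (1.1 for clinic-BF, SD=0.25".
- **Diary, all participants.** Section 5.3, under the heading "During biofeedback therapy", states: "Participants keep a physical or digital bowel diary (bowel habits, stool consistency, symptoms". The listed content does not include a count of incontinent days.
- **Diary, clinic arm (Group A).** Section 5.8: "During treatment period, patients are asked to keep a bowel and food diary". No form or frequency is given.
- **Diary, home arm (Group B).** Section 5.8: "The participants are asked to keep daily bowel and food diaries on the app". The entries go to a cloud server open to the therapist and investigators. Section 2 also describes the app as recording "clinical indicators (symptoms & bowel diary) from user input".
- **Analysis.** Section 5.8 says incontinence episodes will be analysed but does not say where the count comes from.
- **Blinding.** Under Section 5.8, neither therapist nor patient is blinded.

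**The concern.** A decrease needs a start value and an end value obtained in the same way. The protocol arranges this for its other primary outcomes but not for incontinent days. Followed as written, it collects no pre-treatment count that matches what is recorded later.

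The second problem is distinct. If the count does come from the diary, one arm has a prescribed daily app diary and the other has whatever form each patient or clinic chooses. Completeness and recording habits may then differ by arm. Randomisation does not protect against this, because the difference arises after allocation. In an open-label comparison of a self-reported outcome with a narrow accepted gap, it could create or hide a difference between arms.

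**Working it through.** **1. Timing of the primary outcomes, side by side (Sections 3, 5.3 and 5.8)**

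| Primary outcome | Source named? | Start and end measurement? |
|---|---|---|
| Squeeze pressure | Yes, manometry | Yes, pre- and post-therapy |
| Vaizey and Wexner scores | Yes, the questionnaires | Yes, first and last appointment |
| Incontinent days per week | No | No; the only daily instrument runs during therapy |

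The one other baseline entry that could bear on it is the bowel history and symptoms item in Section 5.3, which mentions no incontinent-day count. Sections 5.4, 5.7 and 5.8 run from consent on the day to eligibility and opening the envelope, with no diary period before treatment.

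**2. The diary, by arm**

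| | Group A (clinic) | Group B (home) |
|---|---|---|
| Form | Not fixed; paper or digital permitted | App |
| Frequency | Not stated | Daily |
| Therapist access during treatment | At clinic visits | Remotely, through the cloud |

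**3. The accepted gap**

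Inputs from Section 5.3: decreases of 0.95 and 1.1 days/week, SD 0.25, margin 0.44 SD, n = 30 per arm.

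- From the stated decreases: 1.1 − 0.95 = 0.15 days/week, which is 0.15/0.25 = 0.60 SD, or one day per 1/0.15 = 6.7 weeks.
- From the stated margin: 0.44 × 0.25 = 0.11 days/week, or one day per 1/0.11 = 9.1 weeks.

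The protocol's own power figure of 0.70 at 0.44 SD does not reproduce. With one-sided 0.05 and no true difference, Φ(0.44/√(2/30) − 1.645) = Φ(0.06) = 0.52. That is a separate matter. Only the SD, n and accepted gap are used below.

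**4. What each gap does to the comparison**

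Write the change in an arm as B − (E + d), where B is the baseline count, E the true end count and d the reporting shift of the instrument used at the end.

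- *Baseline gap.* If B is obtained in the same way in both arms before allocation, its error has the same expectation in each. It adds noise and distorts within-arm change, but does not by itself bias the difference between arms.
- *Form gap.* If d differs between arms and B does not carry the same shift, the difference in d passes straight into the between-arm comparison. If B came from the same diary in the same form, a constant shift would cancel, but one that changed over the course would not. The missing baseline therefore removes a safeguard against the form difference.

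**5. Illustration with assumed shifts**

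The documents give no reporting shift, so a range is shown. Assumptions: one-sided 0.05 (the protocol does not state sidedness), n = 30 per arm, SD 0.25 applying to the change, and a margin of 0.15.

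SE = 0.25 × √(2/30) = 0.0645 days/week.

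False non-inferiority rate when the true difference sits at the margin and the shift b favours home: Φ(b/SE − 1.645).

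Power when the arms are truly equal and the shift goes against home: Φ((0.15 − b)/SE − 1.645).

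| Assumed b (days/week) | False non-inferiority rate | Power |
|---|---|---|
| 0 | 0.05 | 0.75 |
| 0.025 | 0.10 | 0.61 |
| 0.05 | 0.19 | 0.46 |
| 0.10 | 0.46 | 0.19 |
| 0.15 | 0.75 | 0.05 |

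**The case against.** The strongest reply is that much of this is inferred, and several stronger readings do go beyond the text.

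- *That the outcome is taken from the diary.* A reader might infer this, but no section says so, and the listed diary content names no incontinent days. What stands is that the source is unnamed and the diary is the only daily record described. Any other intended source would equally need naming.
- *That the decrease is recalled history minus prospective diary.* The protocol specifies no such subtraction. An early diary week could serve as the reference, although it would fall after allocation and after treatment had begun.
- *That the section heading rules out a baseline.* The same heading also covers scores taken at the first appointment, so it is weak evidence alone. The Group A wording in Section 5.8, which ties the diary to the treatment period, is firmer.
- *That the clinic arm uses paper.* Paper is permitted, not prescribed; some or all of that arm could keep a digital diary.
- *That the app diary is prescribed at Site 2.* The sentence sits in the paragraph on the six-session regimen of Site 1, and the Site 2 paragraph does not repeat it. Section 2 describes the diary as an app function generally, so it is likely to apply at Site 2, but this is inference.
- *That only home diaries are seen by the therapist.* Section 5.8 has the therapist review participants' diaries at the end of treatment; only the remote access differs.
- *That one miscounted day per course uses up the margin.* One day in two months (about 8.6 weeks) is 1/8.6 = 0.12 days/week. That is close to 0.11 but below 0.15, and it presumes an average one-day error in one direction, with counting over the whole course.

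The exact diary weeks to be counted could be left to a statistical analysis plan. But no analysis plan can recover a baseline that was never collected, or make two instruments the same afterwards.

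**Conclusion.** The point holds as a defect in data collection that should be corrected. The source of a primary outcome is not named, the plan schedules no matched pre-treatment count for an outcome judged on a decrease, and the diary is specified for one arm only. The first two affect both arms alike and mainly weaken the change score. The third can bear on the comparison between arms.

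The accepted gap is 0.15 days/week, or 0.11 at 0.44 SD, so a modest reporting difference would matter. The documents do not show that such a difference exists, how large it is, or which arm it would favour. The rates under working are therefore a sensitivity range, not an estimate of bias. They also rest on a one-sided 0.05 test, 30 analysed per arm, and 0.25 being the SD of the change.

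**What to change.** Amend Sections 5.3 and 5.8 to:

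1. State that incontinent days per week are counted from the bowel diary, and add that item to the diary content.
2. Use the same items, form and daily frequency in both arms at both sites: either the app's diary module or one common paper form.
3. Define baseline and end-of-treatment windows of equal length, with the baseline window (for example 7 days) completed after consent and before the first training session.

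The cost is up to a week's delay before the first session and minor set-up for the common form. Giving the clinic arm the app would extend the cloud data handling in Sections 7.3 and 7.4 to that arm. Using paper in both arms would set aside one of the app's functions.

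If no run-in is possible, compare end-of-treatment incontinent days per week between arms, adjusted for the baseline incontinence score. This adds no delay, but it replaces the decrease as the outcome, so the Section 5.3 criterion and margin for this outcome must be restated to match. A common diary form becomes essential, because no diary baseline would be there to cancel a constant reporting shift.

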**5.4 Recruitment and Screening**

Patients referred to study sites for BF therapy will be asked to take part in this study. The PIs at their respective sites ([name] and [name]) will determine eligibility. Potential participants are provided with the information sheet and consent form one week before their appointment as part of the standard preparation pack for patients. On the day of the test, [name] or [name] (not involved in patient’s treatment) will engage with the potential participants by going through the patient information sheet with them. During this process the investigator will ensure the potential participant understands the study and risks, answer any questions, and, aware of the risks and how their data will be used.

**5.5 Inclusion criteria**

- Males and females 18 to 65 years
- Diagnosed with urge faecal incontinence or faecal seepage
- Able to provide verbal and written consent

**5.6 Exclusion criteria**

- Pregnant women and the human foetus
- People under the age of 18
- People with a cognitive impairment, an intellectual disability or a mental illness
- Anorectal surgery within the last 3 years
- Presence of active anal fissure and/or symptomatic haemorrhoids
- Individuals with implantable or portable electro-mechanical medical devices (e.g. pacemaker, sacral nerve stimulation impact)

**5.7 Consent Process**

[name] (site 1) and [name] (site 2) will obtain written consent from eligible participants or delegate the duty to [name] (site 1 and 2). Consent will be sought on the day of their study after potential participants have been give project information and opportunity to discuss the study with an investigator. It will be made clear that participation is voluntary and that the participant may withdraw at any stage with no detriment to their health care. Investigator will gauge their understanding by asking the potential participants questions about what they believe they are being asked to do. Investigators will also address any questions that arise from the participants in regards to the study. If the participants have any concerns or questions that arise at any stage in the future, they may contact [name] to further discuss them. Formal consent will be obtained in writing immediately following this as the information sheet and consent form is read by/to the participant, who may then indicate their voluntary participation by signing the consent form. A copy of the consent and information sheet will be provided to the participant to keep.

Participants may wish to withdraw from the study at any time. In the event the participant wishes to withdraw from the study, we will retain all data collected up to the point with withdraw.

**5.8 Study Procedure**

Patients arrive at a study site to undergo routine diagnostic anorectal manometry. If a patient is diagnosed with a functional faecal incontinence and suitable for BF therapy they will be asked to take part in this study. Randomization used permuted blocks of 4 with 1:1 assignment into the parallel study groups described in Section 5.3. Random numbers generated in advance and placed into sequentially numbered opaque envelopes, sealed and used for subject assignment. After screening, and once patients met the study inclusion and exclusion criteria, patients are enrolled into one of the treatment arms, by opening the sealed envelope. The therapist ([name] or [name]) and patient are not blinded to the treatment.

The specialist nurse therapist provides advice regarding bowel habits, exercise, laxatives, dietary fibre and fluid intake, and timed-toilet training during the initial consultation to all participants. The therapist will teach participants how to improve their push effort by using postural and diaphragmatic breathing techniques and instruct them to practice these manoeuvres at home for 15 minutes, three times a day.

*Clinic-based biofeedback using anorectal manometry*

In addition to the aforementioned general instructions, participants receiving clinic-based BF (**Group A**) will be attending a maximum of six in-clinic therapy sessions over 2 months. BF training uses the anorectal manometry. Manometry catheters have several circumferential pressure sensors that straddle the entire anal canal and a proximal sensor placed in the rectum, providing continuous and dynamic spatiotemporal mapping of anorectal pressures. During anorectal BF therapy, a sheath is placed over the catheter and inserted into the anal canal. The system and therapist provides provide visual/audio feedback to the patient and record exercise parameters to establish baseline or evaluate progress. The key BF manoeuvres are:

1. **Rest:** after probe placement, a period of time is given for the patient to relax such that anal sphincter tone returns to basal levels. Anal resting pressure is measured using the averaged resting pressure over the length of the anal canal over a period of 20 seconds. This pressure is a composition of the internal and external anal sphincter and, to a lesser extent, by the hemorrhoidal plexus.
2. **Squeeze and hold:** The patient is asked to squeeze the anus for as long as possible, for a maximum of 30 seconds. By convention, this manoeuvre is performed three times. Both the maximal contractile pressure and endurance times are measured. Ideally, rectal pressure should not increase, because that would imply the patient has contracted the abdominal wall.
3. **Simulated defecation (push):** The patient bear down as if to defecation and attempt to expel the catheter. This manoeuvre should produce sufficient rectal propulsion pressures with simultaneous anal sphincter relaxation (>20% relaxation).

During treatment period, patients are asked to keep a bowel and food diary. During their in-clinic visits, the therapist will provide consultation on the patient’s progress and any changes to clinical indicators.

*Home-based biofeedback using new device*

In addition to the general instructions, patients selected for home-based BF with novel device (**Group B**) will be trained on the use of home-training device by the therapist. For feasibility study at Site 1, participants will use the device in the clinic under supervision for a maximum of six sessions.

Accuracy and repeatability of prototype V2 will be assessed in the first five (n=5) group B participants. Participant manometry parameters (e.g. resting, push, squeeze) will be compared against the prototype data during their first training session. Capabilities of the V2 sensors will compared against previous V1 data [18] to determine if the V2 prototype is suitable for use. If V2 sensors are not deemed suitable, the trial will be temporary suspended while the technical issues are resolved. During this time, the participant will be removed from the study and begin conventional treatment. If V2 sensors are suitable the participant will continue with trial and subsequent sessions.

Group B participants will undergo 6 supervised clinic sessions with the experimental device. After session two, they may also take the device home and continue training during the treatment period. The wireless device contains sensors to measure anal sphincter and rectal pressures. A condom sheath is placed over the probe before it is inserted into the anal canal. The user will download the training program (mobile app) onto their mobile phones, which will guide the user through the required exercises (identical to the clinic-based BF manoeuvres listed above). Participants will be asked to insert the probe and perform training for 5 – 10 minutes daily over a training period of 2 months. Training data is send to a cloud server for therapist to monitor compliance and correct usage. The participants are asked to keep daily bowel and food diaries on the app, this information is sent to the cloud accessible only by the therapist and investigators.

Upon completion of the feasibility study, home-based BF with novel device at Site 2 (Group B) will only undergo one supervised training session with the novel device. Participants then take the device home and continue training unsupervised for the duration of their treatment period. The therapist monitor adhesion remotely through the cloud server and will arrange fortnightly telehealth consultations to provide encouragement and evaluate progress.

At the end of the treatment period, participants in Group B will undergo a short useability interview. The therapist will ask the participant questions regarding the 1. Ease of use, 2. Clarity of instructions, 3. Ease of cleaning, 4. Any additional Issues.

*Data analyses*

At the end of the treatment period participants will return to the clinic for a repeat anorectal manometry study to determine changes in anorectal physiology parameters. The therapist will also review their bowel and food diaries. The therapist will discuss the results with the participants and plan the next course of action.

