**1. SUMMARY**

| **Study Title**: Comparison of anorectal biofeedback therapy delivered by home-based device with clinic-based anorectal manometry in patients with functional defecation disorders  **Aim:** To compare the treatment efficacy of anorectal biofeedback (clinical indicators and physiological parameters) performed with a novel home-based device with conventional therapies in patients with functional faecal incontinence.  **Site Location:**   1. GI Motility Clinic, Camden Hospital, NSW 2570 2. Advanced GI Surgery Unit, Royal Prince Alfred Hospital, NSW 2050   **Planned sample size:**   - Site 1: 40 participants (20 home-based with device, 20 clinic-based manometry) - Site 2: 80 participants (40 home-based with device, 40 clinic-based manometry)   **Inclusion criteria:** Males and females 18 – 65 years old, able to comprehend study and provide written consent. Diagnosed with a functional faecal incontinence and recommended for anorectal biofeedback therapy.  **Study procedures:**  A pilot feasibility study consisting of 40 participants will randomly assigned therapy with the novel device or anorectal manometry (conventional treatment). The conventional treatment group will receive 6 clinical training sessions with standard manometry (30 – 45 minutes each). While the test group will use the novel device at the clinic for 6 supervised training sessions, they may take the device home and continue training in between clinic sessions.  Upon completion of the feasibility study, a larger scale study (n=80) will be conducted. The test group will only receive one training session with the novel device and required to complete the rest of their training unsupervised at home.  **Study duration:** 3-years (36 months) |
| --- |

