The recording and reporting of adverse events will be classified based on their severity (“Negligible”, “Minor”, “Serious”, “Critical”, and “Catastrophic”). All events classified as “minor” or above in severity will be recorded and notified to the Principle investigator ([name]) and site coordinating investigator ([name]). Events classified as “Serious” or above will be will reported to HREA in to form of a “safety report” and trial will be temporarily suspended to investigate cause of event and implement appropriate mitigation strategies (e.g. instructions-of-use, technical updates, update cleaning procedure).

The clinicians involved in this study ([name] and [name]) will be available to help if any adverse events or symptoms occurs during the study. They will be able to provide medical advice and determine the best course of action.

To avoid coercion or inducement, an investigator not directly involved in the participant’s treatment (e.g. [name]) will be explaining the procedure and obtaining informed consent.

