**7.3 Confidentiality and Privacy**

Identifiable participant information will remain on site on the Hospital’s password protected computer. Identifiable information (name, MRN, date of birth) will be kept on a “decoding sheet” in a separate folder to study data, only the PI will have access to the decoding sheet. De-identified health data will be stored on the site network using a data management software (RedCap).

Data collected by the device and app will be sent to a secure cloud server managed internally by Western Sydney University and only accessible by study investigators. This data used entered into RedCap in a non-identifiable form for analysis by investigators. Dissemination of data will in the form of descriptive statistics (e.g. mean±SD) in results and publications.

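### The disclosed fixed block size of 4 makes up to one third of allocations deducible in this open-label trial, an avoidable risk of selection bias

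*Protocol*

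**What the plan says.** Section 5.8 of the protocol fixes the allocation scheme: "Randomization used permuted blocks of 4 with 1:1 assignment into the parallel study groups". Concealment is by envelope: "Random numbers generated in advance and placed into sequentially numbered opaque envelopes, sealed and used for subject assignment". After screening, "patients are enrolled into one of the treatment arms, by opening the sealed envelope". The same section says that the therapist "and patient are not blinded to the treatment".

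Recruitment roles are spread over three sections:

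- **Section 5.4:** the principal investigator at each site "will determine eligibility", and someone not involved in the patient's treatment goes through the information sheet.
- **Section 5.7:** site investigators obtain written consent or delegate that task.
- **Section 7.2:** to avoid coercion, "an investigator not directly involved in the participant’s treatment" explains the procedure and obtains consent.

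Nothing in the protocol varies or withholds the block size, or keeps those who judge eligibility or take consent unaware of earlier allocations.

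**The concern.** Sealed envelopes hide the next card. They do not hide what can be worked out from the cards already opened. With one known block size and equal allocation, once two patients in a block have gone to the same arm, the rest of that block is settled. Because treatment is open, earlier allocations are visible at the site. Section 5.8 also gives therapist and investigators access to the app data of device users, so investigators with that access can tell who is in Group B.

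If someone with a say in eligibility, presentation or timing can foresee the next arm, patients entering the two arms may differ in severity or motivation. That matters here for three reasons. Two of the primary measures in section 3 are subjective. The Site 2 claim is non-inferiority within 0.44 SD (section 5.3). Two investigators are inventors of the device and may have a financial interest (section 8). Differences in unmeasured traits such as motivation could not be repaired in the analysis.

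**Working it through.** The protocol gives no figure for predictability, so there is none to reproduce.

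**Inputs**

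- Block size 4, two home (H) and two clinic (C) places per block: section 5.8.
- 40 participants at Site 1 and 80 at Site 2: section 1. These make 40/4 = 10 and 80/4 = 20 blocks.
- Site 2 starts after Site 1 is complete: sections 1 and 5.8. Each site would then see its own sequence without interruption.
- Assumption: the observer knows the block size, the block boundaries and all earlier allocations at the site.

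**Allocations known with certainty.** There are C(4,2) = 6 equally likely blocks. An allocation is certain when one arm has already used both its places.

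| Block | Certain allocations |
| --- | --- |
| HHCC | 2 (third, fourth) |
| CCHH | 2 (third, fourth) |
| HCHC | 1 (fourth) |
| HCCH | 1 (fourth) |
| CHHC | 1 (fourth) |
| CHCH | 1 (fourth) |

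The total is 8 of 24, or 1/3. Expected numbers are 80 × 1/3 = 26.7 at Site 2 and 40 × 1/3 = 13.3 at Site 1.

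**Best-guess accuracy.** The observer guesses the arm with more places left.

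- First place: 1/2.
- Second: 2/3.
- Third: 1/3 × 1 + 2/3 × 1/2 = 2/3.
- Fourth: 1.

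The sum is 17/6 per block, and 17/6 ÷ 4 = 17/24 = 70.8%, against 50% under simple randomisation.

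**Alternatives.** Fixed schemes were enumerated in the same way. Varying schemes were simulated (1,000 runs at each of N = 40 and N = 80) against an observer who knows the set of sizes but not their order.

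| Scheme | Certain | Best guess right |
| --- | --- | --- |
| Fixed 4 | 33.3% | 70.8% |
| Fixed 6 | 25% | 68.3% |
| Fixed 8 | 20% | 66.6% |
| Random 2, 4 | about 10.5–11% | about 72% |
| Random 2, 4, 6 | about 4% | about 70% |
| Random 4, 6 | about 5.5% | about 69% |
| Random 4, 6, 8 | about 2.3% | about 68% |

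Varying the size removes nearly all of the certainty but little of the guessing advantage.

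**Illustration of the possible effect.** Suppose that every certain allocation (1/3 of each arm on average) were filled by a patient whose expected change is shifted by d SD, upwards in one arm and downwards in the other. The arm means would then differ by d/3 + d/3 = 2d/3. For an assumed d of 0.1 to 0.3 this is 0.07 to 0.20 SD, or 15% to 45% of the 0.44 SD margin. The protocol gives no value for d, and zero is possible.

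**The case against.** Four objections deserve weight.

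1. **Recruitment is partly separated from treatment.** Sections 5.4 and 7.2 have the study explained by someone outside the patient's treatment. A reader might infer that one small team treats, judges eligibility and takes consent. The documents do not support that: names are removed, so overlap of roles cannot be established, and the separate explainer points the other way. What stands is that this safeguard is partial. Its stated purpose is to avoid coercion, section 5.7 lets site investigators take consent themselves, and site investigators decide eligibility.

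2. **The room for steering is limited.** Referred patients receive the study papers one week before their appointment (section 5.4), and most entry criteria in sections 5.5 and 5.6 are factual. Some discretion remains in the judgement that a patient is suitable for biofeedback (section 5.8) and in how the study is presented.

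3. **One third is a ceiling.** A reader might infer that recruiting staff will know a third of allocations. The protocol shows only that these can be deduced by someone who tracks the sequence. A single list interleaved across sites would make fewer of them certain, although running the sites one after the other argues against that.

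4. **The remedy is incomplete.** Best-guess accuracy falls by only about 3 percentage points, as the table shows. That is correct, and it is why the list and the release of allocations also need separating from recruitment.

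It is also fair to say that squeeze pressure is an objective primary outcome, though differences between arms at entry could affect it too, and that the Site 1 pilot is not analysed together with Site 2. Section 8 shows that two investigators invented the device. It does not show that they recruit or know the sequence.

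**Conclusion.** The point holds as a design weakness that should be corrected, chiefly before the non-inferiority stage at Site 2. Fixing and disclosing blocks of 4 in an open-label trial makes up to 33.3% of allocations deducible: about 27 of 80 at Site 2 and about 13 of 40 at Site 1. The arithmetic is exact. Its application rests on an observer knowing the block size and following the earlier allocations in an unbroken sequence at the site. The documents do not show that anyone will do this, and they do not show bias in either direction. The finding is a risk of selection bias that the envelopes do not remove and the separate explainer only reduces.

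**What to change.** In section 5.8, for allocations not yet made:

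- Replace the fixed block size with randomly varying sizes, for example 4, 6 and 8.
- Have a separate list for each site generated by someone outside recruitment and treatment.
- Keep the sizes out of any document available to recruiting staff, including the protocol they work from.
- Open the envelope only after eligibility, consent and baseline scores are recorded. If the RedCap installation named in section 7.3 supports randomisation, the allocation could be released there under the same condition.

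With sizes 4, 6 and 8, certain allocations fall to about 2–3% even if the set of sizes leaks.

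The cost is a new list, a short protocol change and, if envelopes are already prepared, a fresh set for the remaining patients. Arm sizes may differ at the end by up to about 4 patients: if recruitment stops halfway through a block of 8, the worst case is four to none. Fixed blocks of 4 would balance exactly at 40 and 80.
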